##### Cell isolation

PBMCs (peripheral blood mononuclear cells) will be isolated from peripheral blood by centrifugation on a Lymphoprep™ (Fresenius Kabi Norge AS) density gradient. If needed cells will be aliquoted and cryo-preserved in liquid nitrogen, except for the analysis of immune cell composition where freshly isolated cells will be used.

##### Flow cytometry

The identification and quantification of leukocyte subsets will be done by flow cytometric analysis of PBMCs as described before [10]. The BD Cytofix/Cytoperm™ Fixation/Permeabilization Solution Kit with BD GolgiPlug™ (BD Biosciences) will be used for intracellular stainings according to manufacturer’s protocols. Cells will be analyzed on a Navios Flow Cytometer (Beckman Coulter).

##### Markers of autoimmunity

In order to better assess and monitor the potential for autoimmune disease, the serum will be tested for the following markers of autoimmunity: ANA, cANCA, pANCA, anti-dsDNA, anti-TSHR, anti-TPO, RF, anti-CCP, anti-GBM and anti-platelet antibodies. Samples for autoimmunity testing will be obtained before the start of treatment with alemtuzumab and every 6 months thereafter. There will be additional testing in case of other suspected autoimmune diseases.

#### Secondary endpoints

Secondary endpoints will further characterize the T- and B-cell population in the peripheral blood (every 6 months) (see Table 2). Therefore, the activation status of cell surface receptors, as well as expression of co-inhibitory molecules, will be analyzed by flow cytometry. Furthermore, effector functions of CD4 and CD8 positive T cells will be assessed (e.g. cell proliferation, cytokine production, cytolytic activity and intracellular calcium response). Using flow cytometry expression analysis and in vitro models for migration, the migrational capacity will be analyzed. Additionally, high-throughput TCR- and BCR sequencing of the T- and B cell repertoire will be performed concerning the expansion of distinct clones and distribution of CDR3 sequences. To evaluate regulatory T-cell function levels of TGF-ß and IL-10 and the ability to suppress the activation and proliferation of effector T cells will be analyzed.

##### Proliferation assays

Human PBMCs will be labeled with 5 μM carboxyfluorescein succinimidyl ester (CFSE; Invitrogen) according to the manufacturer’s instructions. After stimulation with anti-human CD3 (2 μg/ml; OKT3) and soluble mouse anti-human CD28 (1 μg/ml; eBioscience) for 4 days proliferation will be assessed by flow cytometry. Otherwise, cell proliferation will be assessed using the ATPLite™ Luminescence Assay System (PerkinElmer) according to the manufacturer’s instructions. Luminescence will be measured on a TopCount NXT.

##### Cytokine detection

Appropriate ELISA-Kits will be used to detect cytokine concentrations in cell culture supernatants and serum. Alternatively, fluorescent bead immunoassays (FlowCytomix, eBioscience) will be used to quantify the production of the chemokines and cytokines according to the manufacturer’s instructions.

##### Intracellular calcium imaging

For intracellular calcium imaging experiments lymphocytes will be isolated using magnetic cell separation. All measurements will be performed in HEPES buffer containing (in mM): NaCl, 120; KCl, 2.5; NaH_2_PO_4_, 1.25; HEPES, 30; MgSO_4_, 2; glucose, 10; pH 7.25 and osmolarity will be set to 305 mOsm/kg. Cells will be loaded with 5 μM Fura-2 AM (Invitrogen) for 30 min at 37 °C. After 15 min anti-mouse CD3 (10 μg/ml; clone 145-2C11; ebioscience,) will be added and fluorescence will be measured using a TECAN infinite M200Pro fluorimeter (Tecan Group Ltd.). Excitation will be alternated between 340 and 380 nm and emission will be measured at 509 nm.

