• Collection of peripheral blood and serum for several in vitro and ex vivo assessments (8 × 9 ml EDTA blood, 2 × 9 ml serum) as part of the routine blood assessments (including complete blood count, serum creatinine levels, tests of thyroid function)	• Collection of peripheral blood and serum for several in vitro and ex vivo assessments (8 × 9 ml EDTA blood, 2 × 9 ml serum) as part of the routine blood assessments (including complete blood count, serum creatinine levels, tests of thyroid function)

The clinical study is registered at clinicaltrials.gov (NCT04082260). It will be performed in accordance with the approval of the local ethics committee (Ethik-Kommission der Ärztekammer Westfalen-Lippe und der Westfälischen Wilhelms-Universität Münster, 2014–398-f-S), the requirements of the current German drug law (“Arzneimittelgesetz”), the current legal provisions regarding data protection, and the principals of Good Clinical Practice. All participants are obliged to hand in the signed informed consent form (ICF).

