• Effector functions of CD4 and CD8 positive T cells: - Relative and absolute change from baseline of the results of cell proliferation assays assessed as the percentage of proliferated cells - Relative and absolute change from baseline of cytokine production measurement assessed as concentration - Relative and absolute change from baseline of the cytolytic activity assessed by flow cytometry measurement of MFI and proportion of positive cells regarding Granzyme B, Perforin and CD107a expression - Relative and absolute change from baseline of intracellular calcium response assessed as a ratio	
• Migrational capacity: - Relative and absolute change from baseline MFI and the proportion of positive cells assessed by flow cytometry expression analysis of CD11a, CD31, CD44, CD49d, CCR5, CCR6, CCR7 - Absolute and relative change of cell numbers of migrated cells compared to baseline assessed in an in vitro model by flow cytometry analysis	
• High-throughput TCR- and BCR sequencing of the T- and B cell rep-ertoire concerning the expansion of distinct clones: - Qualitative comparison of the distribution of CDR3 sequences	
• Regulatory T-cell function: - Relative and absolute change from baseline in production of TGF-beta and IL-10 of CD4^+^CD25^+^FOXP3^+^ regulatory T cells - Suppression of T cell proliferation: Relative and absolute change from baseline in responder T cell proliferation assessed by suppression assays	

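### The printed buffer for the intracellular calcium assay contains no calcium salt, so as written the secondary calcium endpoint cannot capture entry of extracellular calcium

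*Protocol article*

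**What the plan says.** Table 2 of the protocol article lists, among the secondary endpoints under effector functions of CD4 and CD8 T cells, "Relative and absolute change from baseline of intracellular calcium response assessed as a ratio". The Secondary endpoints section repeats the item in general terms: "effector functions of CD4 and CD8 positive T cells will be assessed (e.g. cell proliferation, cytokine production, cytolytic activity and intracellular calcium response".

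The method is in the section Intracellular calcium imaging. Lymphocytes are isolated by magnetic separation. The buffer is then specified: "All measurements will be performed in HEPES buffer containing (in mM): NaCl, 120; KCl, 2.5; NaH_2_PO_4_, 1.25; HEPES, 30; MgSO_4_, 2; glucose, 10", with "pH 7.25 and osmolarity will be set to 305 mOsm/kg". Cells are loaded with Fura-2 AM. The stimulus follows: "After 15 min anti-mouse CD3 (10 μg/ml; clone 145-2C11; ebioscience,) will be added and fluorescence will be measured". Excitation alternates between 340 and 380 nm. The section describes no further addition of any kind and cites no earlier publication for the method.

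Table 1 schedules the blood sampling for in vitro and ex vivo work at month 0 and at months 6, 12, 18, 24, 30 and 36.

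**The concern.** In an assay whose measured quantity is intracellular calcium, the calcium content of the bath determines what can be measured. If the bath holds none, none can enter from outside, and any rise in the Fura-2 ratio must come from calcium already in the cell. Table 2 does not restrict the endpoint to that part; it names the calcium response as a whole.

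At stake is the interpretation of the endpoint. Followed literally, the recipe removes the same component at baseline and at every later visit, so neither averaging over patients nor a larger sample restores it. A change under alemtuzumab that lies in calcium entry would be invisible, and a flat result could be taken as evidence that T-cell calcium signalling is unaltered.

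**Working it through.** **Inputs (Intracellular calcium imaging).** NaCl 120, KCl 2.5, NaH2PO4 1.25, HEPES 30, MgSO4 2, glucose 10, all in mM; osmolarity 305 mOsm/kg; pH 7.25.

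**Step 1: is there calcium anywhere in the assay as described?** None of the six solutes contains calcium. The steps after the recipe are dye loading, addition of the anti-CD3 antibody, and reading. None adds calcium, and no other section supplies any. Traces in water or reagents cannot be excluded, so the right description is nominally calcium-free.

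**Step 2: does the stated osmolarity reveal an omitted salt?** The only figure in the text that could test the recipe is 305 mOsm/kg. With full dissociation of the four salts:

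- Sum = 2 × (120 + 2.5 + 1.25 + 2) + 30 + 10 = 251.5 + 40 = 291.5 mOsm.
- Gap to the stated value = 305 − 291.5 = 13.5 mOsm.
- Calcium chloride contributes three particles. An assumed 1 to 2.5 mM adds 3 to 7.5, giving 294.5 to 299.0.
- Base needed to reach pH 7.25 is about 30 / (1 + 10^(pKa − 7.25)) mM. For an assumed HEPES pKa of 7.3 this is 14.1 mM, and for 7.5 it is 10.8 mM. The totals are then 305.6 and 302.3 without any calcium.

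The pH adjustment alone can therefore account for most or all of the gap. The text also says the osmolarity is set, so it may have been adjusted with something unlisted. The figure of 305 neither shows nor rules out a missing calcium salt.

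**Step 3: what happens to the endpoint?** As a simplification, write the response at visit t as S(t) + E(t), where S is release from stores and E is entry from outside. The absolute change from baseline is [S(t) − S(0)] + [E(t) − E(0)]. With no calcium outside, E(t) = E(0) = 0 and the change reduces to S(t) − S(0). The relative change reduces to [S(t) − S(0)] / S(0). An effect confined to E gives an expected change of zero at any sample size. The documents give no values for S or E, so the share lost cannot be computed.

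**Step 4: is S itself assured?** The calcium assay names an anti-mouse CD3 antibody. For the same patients' cells the section Proliferation assays says "After stimulation with anti-human CD3 (2 μg/ml; OKT3) and soluble mouse anti-human CD28 (1 μg/ml; eBioscience) for 4 days", and the section Suppression assay uses the same anti-human CD3. The article does not explain the difference. Store release in response to the stimulus as printed is therefore also not established.

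**The case against.** The strongest reply is that the article condenses a fuller study protocol, which its Limitations section mentions and which is not shown. The reagent list may be incomplete: no pH titrant and no agent for setting the osmolarity is named, yet both were adjusted. A dropped line in a methods paragraph does not show that the laboratory works without calcium. This stands as far as it goes. The documents cannot separate a writing slip from a calcium-free assay. It does not remove the point, because the article did not leave the buffer to another document. It printed a recipe with concentrations down to 1.25 mM and applied it to all measurements. The flow cytometry, migration and receptor-sequencing sections refer to earlier work for their methods; this section does not.

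A second reply is that the same buffer at every visit compares like with like. That is true for whatever component is recorded, but not for the one left out.

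Three stronger readings are tempting and are not supported:

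- A reader might infer that the endpoint is shown to measure only a small release from stores. The documents neither name entry as the target nor give the size of either component.
- A reader might cite the collection tubes, "Collection of peripheral blood and serum for several in vitro and ex vivo assessments (8 × 9 ml EDTA blood, 2 × 9 ml serum", as a reason why no calcium is available. The cells are isolated and separated before measurement in a different buffer, so the tube anticoagulant says nothing about the calcium in that buffer.
- A reader might assume that store release at least is secure. Given the printed clone, it is not.

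**Conclusion.** The point holds in a limited form. As printed, the calcium assay runs in nominally calcium-free buffer and cannot capture entry of extracellular calcium; the ratio could reflect at most store release. This rests on the printed list being what is used. If calcium was present and merely left out of the text, the defect is one of reporting and the data are sound in this respect.

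The reach is narrow. Calcium response is one of four items under effector functions, which is one of six groups of secondary endpoints in Table 2. The Statistical methods section treats all inference as exploratory. Primary endpoints and the sample size calculation are unaffected. The correction is still worth making before further samples are run, because every value is a change from baseline over three years and the buffer has to be known and constant for that change to be interpretable.

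**What to change.** In the section Intracellular calcium imaging:

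1. State the calcium salt and concentration actually used in the measuring buffer. If a calcium-free start is intended, state when and how calcium is added back, and define the ratio on the period after that step.
2. State that the same buffer is used for every batch and visit.
3. If some samples were already measured without calcium, label those results as store release only, and do not pool them with results from a calcium-containing buffer.
4. In the same edit, reconcile the anti-mouse CD3 clone named here with the anti-human CD3 in the proliferation and suppression assays.

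The cost is a few lines of text and a check of the laboratory record. No extra blood, visit or staff is needed. The only possible loss is a narrower reading of calcium results already obtained in calcium-free buffer.

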##### Migration assay

Transmigration assays will be performed with minor modifications as described previously [11]. In brief, HBMEC (human brain microvascular endothelial cells) will be cultured in transwell inserts until they reach confluency. Human PBMCs (each 5 × 10^5^) will be transferred to the HBMEC layer for 14 h. Migrated cells from the lower chamber will be collected and Calibrite beads (BD Biosciences) will be added. Next, human cells will be stained for CD4, CD8, CD14, CD19 and CD56, with the respective monoclonal antibodies and relative cell numbers were determined by flow cytometry.

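### Two secondary functional endpoints are mis-specified: the calcium assay names an anti-mouse CD3 stimulus for human cells, and proliferation allows a read-out that cannot give the percentage defined as the endpoint

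*Protocol article*

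**What the plan says.** All places are in the protocol article.

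- **Calcium.** Under Intracellular calcium imaging: "For intracellular calcium imaging experiments lymphocytes will be isolated using magnetic cell separation". The stimulus follows: "After 15 min anti-mouse CD3" (clone 145-2C11, at 10 μg/ml). Table 2 lists the calcium response, as a change from baseline, among the effector functions of CD4 and CD8 T cells.
- **Proliferation.** Under Proliferation assays, CFSE-labelled PBMC are read by flow cytometry: "After stimulation with anti-human CD3" (OKT3, 2 μg/ml) plus anti-CD28. An alternative is then allowed: "Otherwise, cell proliferation will be assessed using the" ATPLite luminescence system. Table 2 fixes the endpoint as change from baseline in "the results of cell proliferation assays assessed as the percentage of proliferated cells".
- **Suppression.** The Suppression assay section uses sorted cells and the same anti-human CD3 (OKT3).
- **Migration.** Under Migration assay, 5 × 10^5 PBMC per well "will be transferred to the HBMEC layer for 14 h". Migrated cells are stained for CD4, CD8, CD14, CD19 and CD56, beads are added, and relative numbers are obtained by flow cytometry. The Table 2 endpoint is "Absolute and relative change of cell numbers of migrated cells compared to baseline assessed in an in vitro model".

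**The concern.** These endpoints are meant to show functional change beyond cell counts, which is central to the mechanistic aim.

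For calcium, the named stimulus is directed at another species' CD3. It disagrees with the study's own sample source and with the two other CD3-stimulated assays. Either the text is misprinted or the reagent is wrong. In the second case the endpoint would lack a specified human stimulus at every visit.

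For proliferation, one permitted read-out cannot produce the quantity that the endpoint table defines, and no rule says when it applies. If a patient's baseline and follow-up used different read-outs, the change from baseline would have no meaning.

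For migration, a count from a fixed number of mixed cells depends on how many cells of the subset were loaded as well as on how readily they migrate. Alemtuzumab changes the first. The Background reports that B and NK cells return within 3 to 6 months, while T cells stay mostly undetectable for 12 to 18 months.

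**Working it through.** The plan states no figure of its own on this point, so there is none to reproduce. The first two parts are a comparison of text; the third needs arithmetic.

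**1. CD3 stimulus, side by side**

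| Assay | Cells | CD3 antibody |
|---|---|---|
| Proliferation | human PBMC | anti-human, OKT3, 2 μg/ml |
| Suppression | sorted regulatory and responder T cells | anti-human, OKT3, 2 μg/ml |
| Calcium | magnetically separated lymphocytes | anti-mouse, 145-2C11, 10 μg/ml |

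The calcium section does not name the species of its lymphocytes. However, the aim refers to blood of treated patients, the Limitations section says that data come only from blood samples, and animal models are left to further studies. The antibody label therefore conflicts with the cells. Species, clone and concentration are all given, so abbreviation for a journal does not explain the conflict.

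**2. Proliferation read-out against endpoint**

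- Required by Table 2: a percentage of proliferated cells, under CD4 and CD8 effector functions.
- CFSE by flow cytometry gives a value per cell, so a percentage can be formed within a gated subset.
- Luminescence gives one signal per well of PBMC. It has no count of divided cells over all cells, and it cannot be split into CD4 and CD8.

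**3. Migration: how far composition alone could move the count**

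Inputs: 5 × 10^5 PBMC loaded (Migration assay); CD8 count 0.34 falling to 0.175 × 10^9/L at 6 months (Sample size). Assumptions: total PBMC before treatment T = 1.5 to 2.5 × 10^9/L, which the document does not give; other PBMC multiplied by a factor f; migration per cell constant.

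CD8 cells loaded before = 5 × 10^5 × 0.34/T.

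CD8 cells loaded after = 5 × 10^5 × 0.175/(0.175 + f(T − 0.34)).

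Worked at T = 2.0 and f = 1: before, 5 × 10^5 × 0.34/2.0 = 85,000; after, 5 × 10^5 × 0.175/(0.175 + 1.66) = 47,684. The ratio is 0.561, a fall of 43.9%.

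| Other PBMC | T = 1.5 | T = 2.0 | T = 2.5 |
|---|---|---|---|
| unchanged (f = 1) | -42.2% | -43.9% | -44.9% |
| fall 25% (f = 0.75) | -26.1% | -27.5% | -28.3% |
| fall as CD8 does (f = 0.175/0.34 = 0.515) | 0% | 0% | 0% |
| fall 60% (f = 0.4) | +20.8% | +22.7% | +23.8% |

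With constant migration per cell, the migrated CD8 count changes by the same percentage. A percentage taken within a gated subset is free of this effect.

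**The case against.** **Calcium.** A reader might infer that the response will be null or artefactual. The document does not support that. It does not say whether this clone acts on human cells, and a misprint carried over from another method text fits equally well. What stands is the conflict of labels and the need to know which reagent was used.

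**Proliferation.** Nothing says that the two read-outs will be mixed within a patient, and Table 2 already names CD4 and CD8 as the target. Starting from unsorted PBMC does not by itself spoil a gated CFSE percentage. The objection is right on all of this. It does not remove the mismatch between luminescence and the defined endpoint.

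**Migration.** It is tempting to read the 48.5% fall in CD8 count (1 − 0.175/0.34) as the bias, and to conclude that depletion will reappear as reduced migration. That figure is per litre of blood, not a share of PBMC, and a fixed input already removes the effect of total cell loss. Only composition remains, and the table shows that it can act in either direction, although the recovery pattern in the Background makes a fall more likely for T cells. The section is also abbreviated, cites an earlier method, and speaks of relative numbers without saying relative to what, so normalisation may already be intended. Migrational capacity is also assessed by marker expression, which this arithmetic does not touch. This part is therefore a request for clarification.

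**Scope.** All of these are secondary endpoints in a study declared exploratory. The wider reading, that the functional T-cell endpoints as a group are compromised, fails: the suppression assay uses sorted cells with anti-human CD3.

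**Conclusion.** The point holds for two secondary endpoints. The calcium assay names a stimulus that conflicts with the study's human samples and its parallel assays; this follows from the text alone, and its effect on any data cannot be sized from the document. The proliferation section permits a read-out that cannot deliver the Table 2 endpoint.

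Migration is a lesser point, conditional on the counts not already being relative to input. Composition alone could then shift CD8 counts by about -45% to +24%. That range rests on the assumed PBMC totals, on other PBMC falling by 0% to 60%, and on constant migration per cell. It shows what is possible and does not predict a bias.

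These corrections should be made, because the endpoints carry the functional part of the mechanistic aim. The suppression assay and gated CFSE are unaffected, and no sample size or error rate depends on the endpoints at issue.

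**What to change.** 1. **Calcium.** Correct the section to an anti-human CD3 stimulus, consistent with the proliferation and suppression assays. Check laboratory records for the reagent behind any calcium data already collected, and report what was used. Cost: one line and a records check.
2. **Proliferation.** State that the endpoint is the CFSE percentage gated on CD4 and on CD8. Keep ATP luminescence as a descriptive read-out, and never combine the two in a change from baseline. Cost: wording only.
3. **Migration.** Say what the relative numbers are relative to. If they are not relative to input, define the endpoint per subset as migrated cells divided by input cells of that subset. Take input composition from the same fresh or thawed aliquot that was loaded. The Cell isolation section allows cryopreserved cells for assays other than immune cell composition, so percentages from the fresh sample may not describe a thawed input. Cost: wording, plus staining of the input aliquot where that is not already done. No additional blood is needed beyond the planned draws.

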##### Migration assay

Transmigration assays will be performed with minor modifications as described previously [11]. In brief, HBMEC (human brain microvascular endothelial cells) will be cultured in transwell inserts until they reach confluency. Human PBMCs (each 5 × 10^5^) will be transferred to the HBMEC layer for 14 h. Migrated cells from the lower chamber will be collected and Calibrite beads (BD Biosciences) will be added. Next, human cells will be stained for CD4, CD8, CD14, CD19 and CD56, with the respective monoclonal antibodies and relative cell numbers were determined by flow cytometry.

